## Abstract

**Background:**

To cope at their homes, community-dwelling older people surviving a hip fracture need a sufficient amount of functional ability and mobility. There is a lack of evidence on the best practices supporting recovery after hip fracture. The purpose of this article is to describe the design, intervention and demographic baseline results of a study investigating the effects of a rehabilitation program aiming to restore mobility and functional capacity among community-dwelling participants after hip fracture.

**Methods/Design:**

Population-based sample of over 60-year-old community-dwelling men and women operated for hip fracture (n = 81, mean age 79 years, 78% were women) participated in this study and were randomly allocated into control (Standard Care) and ProMo intervention groups on average 10 weeks post fracture and 6 weeks after discharged to home. Standard Care included written home exercise program with 5-7 exercises for lower limbs. Of all participants, 12 got a referral to physiotherapy. After discharged to home, only 50% adhered to Standard Care. None of the participants were followed-up for Standard Care or mobility recovery. ProMo-intervention included Standard Care and a year-long program including evaluation/modification of environmental hazards, guidance for safe walking, pain management, progressive home exercise program and physical activity counseling. Measurements included a comprehensive battery of laboratory tests and self-report on mobility limitation, disability, physical functional capacity and health as well as assessments for the key prerequisites for mobility, disability and functional capacity. All assessments were performed blinded at the research laboratory. No significant differences were observed between intervention and control groups in any of the demographic variables.

**Discussion:**

Ten weeks post hip fracture only half of the participants were compliant to Standard Care. No follow-up for Standard Care or mobility recovery occurred. There is a need for rehabilitation and follow-up for mobility recovery after hip fracture. However, the effectiveness of the ProMo program can only be assessed at the end of the study.

**Trial registration:**

Current Controlled Trials ISRCTN53680197

## Background

Fall-related injuries leading to hospitalization and activity restriction result in adverse health outcomes, mobility limitation and disability which may last years or become permanent [1-3]. For older people, hip fractures are among the most severe consequences of falls [4,5]. Hip fractures cause considerable health care costs during the first post fracture year [6-8]. The cost burden will double or even triple with the subsequent fall and fracture particularly if a home-dwelling person is admitted to permanent institutional care because of the fracture [8,9].

Community-dwelling older persons who survive a fracture need special attention. To cope at their homes safely sufficient mobility and functional ability is needed. Only 40% of hip fracture survivors recover to their pre-fracture ambulatory level and only 20% recover to the pre-fracture level in advanced mobility tasks [3,10]. Safe mobility and participation are challenged by persistent pain [11,12], fear of falling and balance impairments [13,14], lower limb muscle weakness [11], reduced bone mass and impaired bone geometry [15]. Consequently, older community-dwelling people recovering from a hip fracture are at an increased risk for a new fracture, persistent mobility limitation and disability as well as loss of independence in the near future.

Currently there is insufficient evidence on the best practices supporting recovery after hip fracture [16]. The current research knowledge is mostly based on efficacy driven research in which the effects of highly specified short-term interventions without follow-up have been investigated among a homogenous group of hip fracture participants. These studies have been performed under optimal conditions with specifically designed and arranged training protocols and facilities. Previous efficacy studies have shown that rehabilitation programs including intensive and supervised training sessions with resistance and balance training improve mobility [17-20], physical functioning [18-21] and level of physical activity [22] among older community living persons who have suffered a hip fracture. However, the effects on mobility disability remain unclear.

A rehabilitation program that produces significant effects in an efficacy study may not have same effects under real-world conditions [23]. Moreover, persons who are likely to benefit the most from a program including physical activity are usually excluded from these studies. Travelling to organized and supervised sessions on a weekly basis in a gym with the necessary set-up may be too demanding for many fracture patients [19,24]. Therefore, rehabilitation programs aiming to restore mobility after hip fracture need to be implemented and studied in the real-world conditions or close to that. Moreover, participants should not be excluded unless there is an empirical or ethical reason to do so (e.g. possibility for negative side effect of training or main outcomes are impossible to measure) [25]. Home-based individually tailored rehabilitation programs including weight-bearing exercises [26,27], exercises with progressive resistance [28] and a systematic follow-up and support [22] may form the most promising approach to increase the effectiveness of the rehabilitation to prevent mobility disability after hip fracture.

The Promoting Mobility after Hip Fracture (ProMo) study investigates the effects of a year-long individually tailored and home-based rehabilitation program compared to the Standard Care on mobility recovery, physical functional capacity and disability among over 60-year-old community-dwelling men and women who suffered a proximal femoral fracture. The purpose of this article is to describe the recruitment process, design and intervention as well as to present demographic baseline results of this randomized controlled trial.

## Methods/Design

### Context

All Finnish residents have health insurance. In Finland, municipalities are responsible for organizing specialized and primary health care for all people. For example, in Central Finland specialized care is provided by the Central Finland Central Hospital for 23 municipalities with a total population of 273 700. Each municipality organizes primary health care including inpatient rehabilitation, ward care and outpatient clinic for their residents at the local health care centers. After a proximal femoral fracture, patients living in Central Finland are operated at the Central Finland Central Hospital and transferred to the local health care centre of their municipality for inpatient care and rehabilitation typically within the first post-operative days. The inpatient rehabilitation period ranges from one week to few months depending on the health status and care needs.

### Design

This study is a randomized controlled trial (RCT, ISRCTN53680197). Random allocation to the intervention (ProMo) and control (Standard Care) groups were performed after baseline measurements by the statistician, who was blinded to the study participants and their characteristics. The study group assignments were enclosed in sealed envelopes. Men and women and those operated with internal fixation or arthroplasty were randomized by blocks.

All participants were measured at the laboratory four times; at baseline, three, six and 12 months. After that all participants were followed-up for an additional year to collect data on form of dwelling, mobility limitation, physical functional capacity, mood and quality of life with a structured questionnaire. Study design is described in detail in Figure 1.

**Figure 1 F1:**
[figure not shown]
**Study design**.

Pretrial power calculations were based on previously published longitudinal data on mobility recovery after hip fracture. In the study by Visser et al, 45.3% of the community-dwelling participants were independent in more demanding mobility tasks (chair rising, walking one block and negotiating stairs) before the fracture [10]. Twelve months after hip fracture less than half of them (20.7% of the total sample) had regained their pre-fracture level of mobility. The purpose of our study was to restore the pre-fracture level of mobility by the ProMo rehabilitation program. To detect the expected difference (based on percentages 45.3 and 20.7 from the study by Visser et al) between the study groups in mobility recovery at α = 0.05 and β = 0.20, a minimum of 44 subjects was needed in each study group. Sample size was calculated using an online sample size calculator available from (DSS researcher's toolkit, http://www.dssresearch.com/KnowledgeCenter/toolkitcalculators/samplesizecalculators.aspx)

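### The stated 80% power assumes the ProMo arm reaches the cited cohort's full pre-fracture mobility level; partial recovery leaves the trial well short of 80%

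*Protocol article*

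**What the plan says.** The power paragraph under Methods/Design, Design, draws on one published cohort of hip fracture patients. It reports that "45.3% of the community-dwelling participants were independent in more demanding mobility tasks (chair rising, walking one block and negotiating stairs) before the fracture". It then reports that twelve months after the fracture "less than half of them (20.7% of the total sample) had regained their pre-fracture level of mobility".

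These two figures become the "expected difference (based on percentages 45.3 and 20.7" between the study groups. The reason offered is the trial's aim: "The purpose of our study was to restore the pre-fracture level of mobility by the ProMo rehabilitation program". The error rates are given as "at α = 0.05 and β = 0.20", without saying whether the test is one-sided or two-sided, and the result is that "a minimum of 44 subjects was needed in each study group".

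The Discussion reports that 81 people were randomised and accepts that the target was not fully reached. The operation counts in Table 1 give the split: 19 + 15 + 6 = 40 ProMo and 19 + 18 + 4 = 41 control. Main outcomes gives the one-year primary outcome as mobility limitation, assessed by interview on five tasks.

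**The concern.** The two percentages are a before-and-after contrast within a single cohort that did not receive ProMo. The calculation uses them as a between-arm treatment effect. The 20.7% is a reasonable guess at a standard-care rate. The 45.3% is not a treated recovery rate from any study; it is the level from which that cohort declined. The only link between the two uses is the aim of restoring pre-fracture mobility, and an aim is not an expected effect.

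The stated power therefore belongs to the case in which the programme reverses the cohort's entire net loss. A programme with a real but partial benefit would have much lower power, and the article gives no figure for that case. A reader who takes the 80% at face value could read a non-significant 12-month result as evidence that the programme does not work.

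**Working it through.** **Inputs.** From the power paragraph: ProMo rate p1 = 0.453, control rate p2 = 0.207, α = 0.05, power 0.80, 44 per group. From Table 1 and the Discussion: 40 ProMo and 41 control randomised. Sidedness is not stated, so both are shown.

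**What the rates imply.** Difference: 0.453 − 0.207 = 0.246. Recovery among the previously independent under usual recovery: 0.207/0.453 = 0.457, or 46%. Recovery implied for ProMo, if the cohort's 45.3% share applies: 0.453/0.453 = 100%.

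**Reproducing the 44 (pooled z-test).** The formula is n = [z_α√(2p̄(1−p̄)) + z_β√(p1(1−p1) + p2(1−p2))]² / (p1−p2)², with p̄ = 0.330.

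- √(2 × 0.330 × 0.670) = 0.665, and √(0.2478 + 0.1642) = 0.642.
- One-sided: (1.645 × 0.665 + 0.842 × 0.642)² / 0.0605 = 44.1, so 45 when rounded up. The arcsine formula gives 43.7, so 44.
- Two-sided: (1.960 × 0.665 + 0.842 × 0.642)² / 0.0605 = 56.2, so 57.

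**Power at 44 per group.** Power = Φ[(p1 − p2 − z_α·SE0)/SE1], with SE0 = √(0.330 × 0.670 × 2/44) = 0.1002 and SE1 = √(0.4119/44) = 0.0968.

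- One-sided: (0.246 − 1.645 × 0.1002)/0.0968 = 0.84, power 79.9%.
- Two-sided: (0.246 − 1.960 × 0.1002)/0.0968 = 0.51, power 69.6%.

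The plan's figure is therefore reproduced, but only as a one-sided 5% calculation.

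**Power at 40/41, no dropout, control fixed at 20.7%.** The ProMo rate is 0.453 × f, where f is the share of previously independent ProMo participants who recover. The values of f below 100% are assumptions, and this form takes the cohort's 45.3% share to apply to this trial. The half-gap row is 0.207 + 0.246/2 = 0.330 and does not need f.

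| Scenario | ProMo rate | One-sided | Two-sided |
|---|---|---|---|
| Full restoration (f = 100%) | 45.3% | 77% | 66% |
| f = 95% | 43.0% | 70% | 58% |
| f = 90% | 40.8% | 63% | 50% |
| f = 80% | 36.2% | 46% | 34% |
| Half the gap closed | 33.0% | 35% | 24% |
| f = 70% | 31.7% | 30% | 20% |
| f = 50% | 22.7% | 8% | 4% |

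At the planned 44 per group, closing half the gap gives about 37% one-sided or 25% two-sided. Reaching 80% power for that effect needs 160 or 203 per group.

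**Minimum detectable rate.** Solving the power formula for 80% at 40/41 against 20.7% gives a ProMo rate of 46.5% one-sided or 50.0% two-sided. Both exceed 45.3%. At 44 per group, one-sided, the solution is 45.3%, which is the plan's own case.

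**The case against.** The strongest reply is that nothing is hidden. The paragraph says where both percentages come from and why they were chosen, and under a one-sided test its arithmetic is sound. The missed target is admitted in the Discussion. Recruitment is over, so the sample cannot be changed. All of that stands: this is an optimistic, disclosed assumption and not a calculation error.

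Three separate matters also need to be kept apart: the choice of 45.3%, the unstated sidedness, and 81 randomised instead of 88. Much of the drop from 80% to 66% at full restoration comes from the last two. Only the fall below the full-restoration row is due to the effect assumption. On the convention that reproduces 44, the required rate at 40/41 exceeds 45.3% by only 1.2 points.

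A reader might infer more than the documents support:

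- **That any partial recovery leaves power between 10% and 50%.** It does not. At 40/41, f = 95% gives 70% or 58%, and f = 50% gives 8% or 4%.
- **That 45.3% is a hard ceiling in this trial, so that no attainable effect has 80% power, or that about 55% of participants could never respond.** The 45.3% describes an outside cohort. This trial's pre-fracture share is not given, and its eligibility criteria could make it different. If it were 55% or 60% (assumed), a 45.3% ProMo rate would mean 82% or 76% recovery. Main outcomes also does not define the endpoint as regaining pre-fracture independence, nor restrict it by pre-fracture status.
- **That the Background uses the wrong denominator when it says "only 20% recover to the pre-fracture level in advanced mobility tasks".** A share of all survivors agrees with 20.7% of the total sample, so no slip is shown.

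**Conclusion.** The point holds as a weakness in the design assumption. The stated power rests on the ProMo arm attaining the cited cohort's full pre-fracture level, while 46% of previously independent people recover under usual conditions. With the numbers actually randomised, even that effect has 77% power one-sided or 66% two-sided before any dropout. An effect half as large has about 35% or 24%.

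These figures assume a 20.7% control rate, a pooled z-test on a binary 12-month outcome and no losses. The rows by recovery fraction also assume that the cohort's 45.3% share carries over to this trial. Other analyses named under Data analysis, such as those using repeated or continuous measures, are not covered by these figures. The consequence is for interpretation: a non-significant 12-month binary comparison would say little about whether ProMo has a worthwhile partial effect.

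**What to change.** In the power paragraph, state that 45.3% represents full restoration to the cited cohort's pre-fracture level, and state the sidedness of the test. Restate power for 40/41 at full restoration and at partial recovery (for example half the gap, and 80% and 90% of the previously independent), and give the minimum detectable ProMo rate of 46.5% one-sided or 50.0% two-sided.

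Report the 12-month between-group difference in mobility limitation with its 95% CI, so that a non-significant result is not taken as absence of effect. Add a supportive ordinal analysis of the five interview tasks listed under Main outcomes, adjusted for baseline, because it uses improvement short of full recovery. The article lists the tasks but describes no score, so the grading has to be specified before results are seen.

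The cost is a few sentences, one extra analysis of items already collected, and a less favourable sample-size justification. No new participants or measurements are needed.

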### Control condition; Standard care

At baseline, information on standard care after the hip fracture was collected by interviewing all participants with structured questions on advice and recommendations concerning rehabilitation they had received at discharge from hospital and/or health care centre. Seventy percent of all participants obtained a written home exercise program with no difference between the intervention and the control groups (68% vs. 71%, p = 0.813). From those who received a home exercise program, 70% exercised every day, 21% on weekly basis and 9% few times a month or not at all. Typically the program included five to seven exercises including ankle flexion and extension, knee flexion and extension, and hip abduction and extension in supine, sitting and/or standing positions with no additional resistance. None of the participants were followed up for the home exercises and the program was not updated. Of all participants 12 received a referral to physiotherapy (5 in the intervention and 7 in the control group) while the rest did not get any further instructions regarding rehabilitation.

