### Data analysis

Means, standard deviations and frequencies for the demographic variables were calculated. Normality of the distributions was tested with Shapiro-Wilkinson test. The significance of differences between the intervention and control group was tested by cross-tabulation and chi-square tests in the case of discrete variables, by Student's t-test for independent samples for normally distributed data and by Mann-Whitney U-test for non-normally distributed continuous data. Association between variables was analyzed using Pearson correlation coefficient. Determinants for mobility limitation and physical disability will be assessed by linear and logistic regression analysis and the theoretical pathway to mobility limitation and physical disability by structural equation modeling. The effects of ProMo will be assessed by intention-to-treat principal using repeated measures ANOVA, covariance analysis and linear mixed models for continuous variables and by general estimation equation for categorical variables.

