The recruitment process of this study included eligibility screening in multiple phases and there was close collaboration with clinicians at the local hospital and health care centers. In total, 296 patients who fulfilled the inclusion criteria were identified and informed about the study at the hospital. From those approximately half (n = 161) were interested in and further informed about the study. From those who expressed initial interest 84% (n = 136) signed informed consent and were enrolled in the study. This was regarded as a sufficient number of participants, allowing a 35% attrition rate, ending with 44 in each study group. Because our participants were recruited at the clinic (health care centre) prior to discharge to home, we set our safety margin in the attrition rate higher than 20% which was recommended by Ferrucci et al in their consensus report [56]. We expected some changes in health status, living conditions and willingness to participate to occur already before the baseline measurements. Accordingly, 26% were further excluded due to poor health, alcoholism and living conditions and 15% declined participation mostly due to poor self-rated health and tiredness (Figure 1). Finally, 81 men and women were assessed at baseline and randomly assigned into ProMo -intervention and control groups. Despite of careful planning of the study and target of the recruitment period from 24 to 33 months, we did not completely reach the estimated number needed for this study. However, as the intervention is home-based and individually targeted and the main outcomes can be assessed at the participants' home, we trust that the additional drop-out will be small. The demographics of our study participants is comparable to earlier studies involving community-dwelling older people recovering from hip fracture; the majority of them are women and the mean age is close to 80 [57].

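### The sidedness of alpha is not stated, and 44 per group reproduces only for a one-sided 5% test; a two-sided test needs about 57 per group

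*Protocol article*

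**What the plan says.** The power paragraph of the Design section takes two percentages from a published longitudinal study of recovery after hip fracture. In that study 45.3% of community-dwelling participants managed the more demanding mobility tasks before the fracture, and 20.7% of the total sample had regained that level at twelve months. The two figures serve as the expected rates in the two arms, and the paragraph concludes that, to detect the difference between the groups "in mobility recovery at α = 0.05 and β = 0.20, a minimum of 44 subjects was needed in each study group". On the tool it says only: "Sample size was calculated using an online sample size calculator". Neither here nor elsewhere does the article use the term one-sided or two-sided.

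The Data analysis section says that the effects of the programme will be assessed by intention to treat, "using repeated measures ANOVA, covariance analysis and linear mixed models for continuous variables and by general estimation equation for categorical variables".

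The Discussion calls 136 consenting patients sufficient because 35% attrition would still leave 44 per group. It then reports 81 randomised and concedes that "we did not completely reach the estimated number needed for this study". Table 1 gives the arm sizes as up to 40 (ProMo) and 41 (control), and its counts by type of operation add to the same totals (19 + 15 + 6 = 40; 19 + 18 + 4 = 41).

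**The concern.** An alpha of 0.05 printed without qualification is normally read as two-sided. Read that way, the rates, alpha, beta and group size in the Design section do not fit together: the stated rates need a clearly larger trial than 44 per group.

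Two things depend on this. The 80% is the only power figure the article gives, and it concerns mobility recovery, the one-year primary outcome. The Discussion also builds on the 44: it is the basis for treating 136 consents as enough and for presenting 81 randomised as a small miss. If the comparison is two-sided, both statements are too favourable.

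**Working it through.** **Inputs.** p1 = 0.453, p2 = 0.207, difference 0.246, alpha 0.05, beta 0.20 and equal groups (Design); 40 and 41 randomised (Table 1); 136 consented with a 35% attrition allowance (Discussion).

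**Step 1. Reproduce the 44.** Per group,

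n = [z_α·√(2·p̄·q̄) + z_β·√(p1q1 + p2q2)]² / (p1 − p2)²

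with p̄ = 0.33, √(2 × 0.33 × 0.67) = 0.6650, √(0.2478 + 0.1642) = 0.6418, z_β = 0.8416 and (0.246)² = 0.0605.

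- One-sided, z_α = 1.645: (1.0938 + 0.5402)² / 0.0605 = 44.1.
- Two-sided, z_α = 1.960: (1.3033 + 0.5402)² / 0.0605 = 56.2, so 57 per group and 114 in total.

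**Step 2. Could another formula give 44 two-sided?**

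| Variant | One-sided 5% | Two-sided 5% |
|---|---|---|
| Pooled under the null (as above) | 44.1 | 56.2 |
| Unpooled variance | 42.1 | 53.4 |
| Average-rate variance | 45.2 | 57.4 |
| Arcsine | 43.7 | 55.5 |
| Continuity-corrected, rounded up | 52 | 65 |

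The one-sided column without continuity correction surrounds 44. The smallest two-sided value, rounded up, is 54. Rounding or choice of formula cannot close a gap of 10 or more per group.

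**Step 3. Power at the stated and achieved sizes.**

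- 44 per group: √44 × 0.246 = 1.6318. One-sided, (1.6318 − 1.0938)/0.6418 = 0.838, power 79.9%. Two-sided, (1.6318 − 1.3033)/0.6418 = 0.512, power 69.6%.
- 40 and 41: the null standard error is 0.1044 and the alternative standard error 0.1010. Two-sided, (0.246 − 1.960 × 0.1044)/0.1010 = 0.41, power 65.9%. One-sided power is 76.9%.

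Exact enumeration of the two-sided chi-square test gives 71.3% (44/44) and 66.6% (40/41). Fisher's exact test gives 62.3% and 63.2%.

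**Step 4. Which sidedness do the documents suggest?** No one-sided hypothesis is declared. Analysis of variance, covariance analysis, mixed models and generalised estimating equations are non-directional as normally run. The printed baseline p-values also behave as two-sided:

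- Haemoglobin at baseline, 127.4 ± 12.7 against 130.1 ± 13.1, taking n = 40 and 41: t = 2.7/2.867 = 0.94, two-sided p = 0.349 (one-sided 0.175). Table 1 prints 0.351.
- Home exercise programme, reported "with no difference between the intervention and the control groups (68% vs. 71%, p = 0.813": the counts 27/40 and 29/41, inferred from the percentages, give a two-sided Fisher p of 0.8127.

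**Step 5. The Discussion's use of the 44.** 136 × 0.65 / 2 = 44.2, so the recruitment figure rests on 88 in total. Against 88 the shortfall is 88 − 81 = 7. Against 114 it is 114 − 81 = 33. With the same attrition allowance, 114/0.65 = 175.4, so 176 consents would have been needed instead of 136.

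**The case against.** The strongest defence is that no two printed figures collide. The Design section never says two-sided, 44 is a valid answer under a one-sided test, and the stated aim of restoring mobility is directional. A condensed article may also leave sidedness to a fuller document. This stands to the extent that the fault begins as an unstated setting and not as a slip in arithmetic. It does not clear the passage. The article chose to print complete inputs and a result, and under the conventional reading of alpha that result is wrong. If a one-sided test was meant, a reader has to be told so in order to interpret the 44.

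A reader might infer that the article establishes a two-sided 12-month test as fact. It does not. The recomputed p-values are baseline comparisons, which have no direction to test, and show the authors' practice only. The counts behind the home exercise p-value are back-calculated: together they give 56/81 = 69.1%, where the text says seventy percent, and they match Fisher's test although the Data analysis section names chi-square. The better evidence is the list of non-directional effect methods together with the absence of any declared one-sided test, and that too is an inference.

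A reader might also take 66% as the power of the planned analysis. The documents do not support that. Generalised estimating equations are planned for categorical outcomes and there are repeated visits; the power of that model depends on covariates and within-person correlation that are not given. The two-proportion figure is the right check on the sample-size sentence, and no more than that.

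Finally, the Discussion admits a shortfall and does not claim 80% power for 81 participants. That is fair. What remains is that the shortfall is measured against the one-sided target.

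**Conclusion.** The point holds as one of unstated sidedness with a definite numerical consequence. The 44 per group matches a one-sided 5% test (79.9% power) and no two-sided one. Under two-sided testing, the better supported reading, the same inputs need about 57 per group, 114 in total. Power is then about 70% at 44 per group and about 66% at 40 and 41, so the type II error is roughly 30% to 34% and not the stated 20%. The trial stands 33 participants below that requirement, and not 7.

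This rests on the article's own rates, on complete 12-month data (any loss lowers power further), and on an unadjusted comparison of two proportions at one time point. That the 12-month test is two-sided is inferred. It does not follow that a null result will be misread, or that the article must prescribe how one is reported; those matters go beyond the error.

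**What to change.** Do not enrol more; correct the text in two places.

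- **Design, power paragraph:** state that 44 per group corresponds to a one-sided 5% alpha, that the 12-month comparison is two-sided, and that 57 per group would be needed for 80% two-sided power at the stated rates. Because two-sidedness is inferred here, the authors should confirm it when they make the statement.
- **Discussion, recruitment paragraph:** restate the shortfall as 81 randomised against 114 instead of 88, with about 66% power at the stated rates before any loss, labelled as an unadjusted two-proportion approximation.

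The cost is wording and a less favourable power figure. No patients, visits, data or analyses are added.

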### Characteristics of the participants

Table 1 summarizes the demographics, physical characteristics, health, living habits, fracture status and the type of operation in the total sample and in the intervention and control groups. No significant differences were observed in any variable between the study groups.

**Table 1 T1:** Demographics, health and hip fracture status among over 60-year-old men and women after a recent hip fracture (Mean ± SD, frequency)

	All (n = 76-81)	ProMo (n = 38-40)	Control (n = 38-41)	p*
Age, yr	79 ± 7	80 ± 8	79 ± 6	0.251
Body height, cm	160.6 ± 8.9	160.9 ± 8.9	160.3 ± 9.1	0.785
Body weight, kg	65.8 ± 11.5	65.8 ± 11.9	65.9 ± 11.3	0.968
BMI	25.5 ± 3.8	25.3 ± 3.6	25.6 ± 3.9	0.710
Poor self-rated health, %	41	43	39	0.823
Number of chronic diseases, n	3 ± 2	3 ± 2	3 ± 2	0.581
MMSE	26 ± 3	26 ± 3	26 ± 3	0.686
BDI-II	9 ± 6	9 ± 6	8 ± 6	0.335#
hCRP at baseline	7.7 ± 9.9	8.4 ± 11.1	7.1 ± 8.6	0.855#
Hb at baseline, g/l	128.7 ± 12.9	127.4 ± 12.7	130.1 ± 13.1	0.351
Lowest Hb after operation, g/l	98.0 ± 13.2	97.5 ± 11.1	98.5 ± 15.0	0.795#
Smoking, %				0.382
- Never	79	85	73	
- Former	12	10	15	
- Current	9	5	12	
Living alone, %	59	60	59	1.000
Level of education Elementary school or less, %	49	54	44	0.502
Income, €/month	1363 ± 828	1321 ± 637	1408 ± 998	0.965#
Physical activity, % Sedentary	92	95	90	0.675
Fracture status				
Fall related fracture, %	88	90	85	0.737
Site of fracture, %				0.645
- Femoral neck	64	68	61	
- Pertrochanteric	36	32	39	
Type of operation, n				0.719
- Internal fixation	38	19	19	
- Hemiarthroplasty	33	15	18	
- Total arthroplasty	10	6	4	

*Independent t-test for normally distributed continuous variables, Chi-square for discrete variables

#Mann-Whitney U for non-normally distributed continuous variables

The mean age of the participants was 79 (SD ± 7) years and 78% of the participants were women. More than half of the subjects were living alone. Poor self-rated health was reported by 41% of the total sample. The average number of chronic diseases was 3 ± 2. The mean MMSE value was 26 ± 3 and that of the BDI-II 9 ± 6. Offending pain in lower back, hip or knee region on the fractured side was reported by 46% of the participants. The corresponding value for the non-fractured side was 37%. Nine percent of the participants were current smokers and 92% were rated sedentary.

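### The 44 per group reproduces only with a one-sided 5% alpha, which the article does not state; at two-sided 0.05 the same comparison has about 70% power at 44 per group and about 66% at the 40 and 41 randomised

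*Protocol article*

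**What the plan says.** In the protocol article, Methods/Design, Design (the text under Figure 1), the power calculation rests on a published cohort of mobility recovery after hip fracture. The group rates are 45.3% and 20.7%, and the result is that "at α = 0.05 and β = 0.20, a minimum of 44 subjects was needed in each study group". The number came from an online calculator. Neither that paragraph nor Data analysis says whether alpha is one-sided or two-sided.

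The Discussion returns to the number. It calls 136 enrolled sufficient, "allowing a 35% attrition rate, ending with 44 in each study group". It then reports that 81 were assessed at baseline and randomised (Table 1 shows up to 40 and 41 per group), and concedes that "we did not completely reach the estimated number needed for this study". Because the outcomes can be assessed at home, it adds that "we trust that the additional drop-out will be small". No power is given for the sample obtained.

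**The concern.** A reader who sees alpha 0.05 and beta 0.20 with no qualifier will assume a two-sided test at 5% with 80% power. Under that convention 44 per group is too few for these rates.

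The Discussion presents the shortfall as 81 against 88, a miss of 7. Against the two-sided requirement of 114 the miss is 33. The assumed effect is also very large, since it has the intervention group regain the cohort's whole pre-fracture rate of independence. If the power to detect even that effect is nearer two in three than four in five, a null 12-month result could be over-read as evidence of no benefit.

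**Working it through.** **Inputs.** From Design: p1 = 0.453, p2 = 0.207, alpha = 0.05, power = 0.80, stated n = 44 per group. From Table 1 and the Discussion: 40 and 41 randomised, 136 enrolled, 35% allowance. Equal allocation is used for the sample sizes.

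**Formula (pooled variance under the null).**

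n = [z_a × √(2 × p̄ × (1 − p̄)) + z_b × √(p1(1 − p1) + p2(1 − p2))]² / (p1 − p2)²

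- p̄ = (0.453 + 0.207)/2 = 0.330, so √(2 × 0.33 × 0.67) = 0.665
- √(0.453 × 0.547 + 0.207 × 0.793) = √0.4119 = 0.642
- (0.246)² = 0.0605
- z_b = 0.8416

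**Reproducing the stated 44.**

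- One-sided, z_a = 1.645: (1.094 + 0.540)² / 0.0605 = 2.670 / 0.0605 = **44.1**
- Two-sided, z_a = 1.960: (1.303 + 0.540)² / 0.0605 = 3.399 / 0.0605 = **56.2**, so 57 per group and 114 in total

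**Is this an artefact of one formula?**

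| Formula | One-sided | Two-sided |
|---|---|---|
| Unpooled | 42.1 | 53.4 |
| Arcsine | 43.7 | 55.5 |
| Pooled, as above | 44.1 | 56.2 |
| Pooled variance in both terms | 45.2 | 57.4 |
| Pooled with continuity correction | 52 | 65 |

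The one-sided formulas without continuity correction give 42 to 45, around the stated 44. The smallest two-sided requirement, rounded up, is 54.

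**Power (same pooled formula, solved for power).** At 44 per group, (p1 − p2)√n = 0.246 × 6.633 = 1.632.

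- One-sided: (1.632 − 1.094)/0.642 = 0.838, power **79.9%**
- Two-sided: (1.632 − 1.303)/0.642 = 0.512, power **69.6%**

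| Sample | One-sided 0.05 | Two-sided 0.05 |
|---|---|---|
| 44 and 44 | 79.9% | 69.6% |
| 40 and 41 (randomised, no later loss) | 76.9% | 65.9% |
| 36 and 37 (10% loss, assumed) | – | 61.3% |
| 34 and 35 (15% loss, assumed) | – | 58.8% |

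Exact enumeration of the uncorrected chi-square test gives two-sided power of 71.3% at 44 and 44, and 66.6% at 40 and 41. Fisher's exact test would give about 62% to 63% in both cases.

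**Where the gap comes from.** At 44 per group, sidedness costs 79.9 − 69.6 = 10.3 points. Going from 44 and 44 to 40 and 41 costs 69.6 − 65.9 = 3.7 points two-sided, or 79.9 − 76.9 = 3.0 one-sided.

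**Attrition allowance.** 136 × 0.65 = 88.4, which gives the 88 (44 per group). Loss before randomisation was 136 − 81 = 55, and 55/136 = 40.4%. This agrees, to rounding, with the 26% excluded and 15% declined in the Discussion. The loss before randomisation alone exceeded the 35% allowed.

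**The case against.** The strongest reply is that the article contains no arithmetic error. It states only alpha and beta, and with a one-sided alpha 44 per group gives 79.9% power, so the inputs and the result agree. That stands as far as it goes. The calculator's settings are not in the document, so one-sidedness is inferred, and the pooled 44.1 would strictly round up to 45. The defect is that the published figure fits only a convention that the article neither declares nor justifies.

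Four stronger readings are tempting, and the document does not support them.

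- *The article claims 80% power for the 81 randomised.* It does not. Beta = 0.20 is attached to 44 per group, and the Discussion openly reports the shortfall in numbers. What it leaves unsaid is the effect on power.
- *The trial's power is 66%.* That figure is for an unadjusted comparison of two proportions at one time point, which is the calculation the article published. Data analysis plans generalised estimating equations for categorical outcomes, with visits at baseline, 3, 6 and 12 months. The 3- and 6-month primary outcome, the Short Physical Performance Battery, is outside this calculation.
- *The efficacy test is known to be two-sided because the reported p-values are.* Those p-values do appear two-sided. For baseline haemoglobin, the difference is 2.7 and its standard error is √(12.7²/40 + 13.1²/41) = 2.87, which gives p = 0.349 two-sided against 0.351 printed. But they are baseline comparisons and do not fix the sidedness of the efficacy analysis.
- *The 35% was meant only for loss before randomisation.* The Discussion says that some change was expected before baseline already, which suggests a general margin. That it was used up by then is what happened, not its stated purpose.

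The article also gives a reason to expect little later loss: under Quality assurance, self-reports and the performance battery can be collected at home. The 10% and 15% losses above are therefore illustrations. An unseen analysis plan could settle sidedness, but it would not change a published set of alpha, beta, rates and n that fits only the one-sided case.

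**Conclusion.** The point holds. For 45.3% against 20.7% at alpha 0.05 and 80% power, 44 per group is a one-sided result, and two-sided the pooled requirement is 57. For that simple comparison, two-sided power is about 70% at the planned size and about 66% at 40 and 41, roughly a one in three chance of missing the assumed effect. On the one-sided basis the randomised sample gives 77%. Most of the gap comes from sidedness and the smaller part from the disclosed under-recruitment. No attrition margin remained after randomisation, so any loss by 12 months lowers these figures further, to about 59% to 61% if 10% to 15% were lost (an assumption).

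The conclusion rests on the article's own rates and on a normal-approximation comparison of two proportions. It corrects the published calculation and makes no claim about the power of the planned longitudinal models.

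**What to change.** In the power paragraph under Design:

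- State that 44 per group corresponds to a one-sided 5% alpha, and that a two-sided 5% test needs 57 per group (114 in total) by the pooled formula.
- Give the two-sided power for the simple two-proportion comparison as about 70% at 44 per group.

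In the Discussion, beside the admission of the shortfall:

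- Give the two-sided power at 40 and 41 as about 66% before later loss, and about 59% to 61% if 10% to 15% are lost by 12 months, labelled as an assumption.
- Note that the 35% allowance was exhausted before randomisation (55 of 136, 40%), so it leaves no margin for loss during follow-up.

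The cost is wording only. No patients are added, and no treatment or analysis changes. The downside is a less favourable stated power.
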